**No** **Yes: If yes; describe the plan**

All identifiable data will be stored in a locked office in Lusaka; only de-identified data will be entered electronically and used for analysis.

- 1. **Are there any anticipated circumstances under which participants will be withdrawn from the research without their consent?**

**No** **Yes: If yes; describe the circumstances as well any associated procedures to ensure orderly termination**

1. **Data/Statistical Analyses Plan**
   1. **Briefly describe the plan for data analysis (including the statistical method if applicable)**

All outcome variables will be compared between treatment and control groups, controlling for baseline covariates observed. To control for within-school correlations, all standard errors will be clustered at the school level.Qualitative data will be analyzed using Grounded Theory, beginning with open coding, and following an iterative coding process.13 First, we will subject all data (SHW interviews, school administrator interviews, and both mother and student FGDs) to an open-coded process without prior assumption of theoretical frameworks. From this, key themes will be deduced and a codebook of these themes will be created. Codes will be generated and assessed using the qualitative analysis program NVivo.

- 1. **Is there a sample size/power calculation?**

**No** **Yes: If yes; describe the calculation and the scientific rationale, and, if applicable, by site and key characteristics such as participant demographics**

We expect a total sample size of approximately 1120 students across the 14 schools. The primary outcome will be pupil health, measured by the presence of any acute or chronic infection. The study is powered to detect a decline in infection prevalence from an expected baseline level of 0.50 to 0.35, assuming a design effect of 2 as well as an attrition rate of 10% over the study period. The secondary outcome of the study is academic performance; the primary measure we will use is days of school missed; the study is powered to detect a 20% increase in the proportion of students not missing any schooling.

1. **Recruitment Methods**
   1. **Does the study involve the recruitment of participants?**

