**2.2 Describe the significance of the research, and how it will add to existing knowledge**

While free health care is provided for children under five years of age in Zambia, research on the health and well-being of the school-aged population in Zambia is limited. The newly designed SBHP currently piloted in 7 schools in Lusaka offer a potentially effective way to improve the health of students in Lusaka and elsewhere in the country; the aim of this project is to assess the effectiveness of these programs.

In our literature review, we could not identify any other program that utilizes a model similar to the SBHP program; for this reason among others, understanding if this innovative program is achieving its intended purpose is particularly important.

While improving population health through schools has long been a focus of the Zambian Ministry of Education, the SBHP model represents a new approach. School is an appropriate setting for a health intervention in Zambia because school-aged children are the population most affected by infectious diseases, and primary school attendance is as high as 94%.1 Additionally, no other known program utilizes a model similar to HK/BF’s SHW program in which teachers may make referrals to health centers. One program conducted by the Zambian Ministry of Education focused on strengthening teachers’ “professional skills” with in-service teacher trainings and follow-up “professional support”.11 While this program did work on developing leadership skills, it did not emphasize teacher empowerment, a point of the SHW program. Other school-based health interventions in Zambia focus mainly on health curriculum, such as the Nutrition Education in Basic Schools (NEBS) project also led by the Zambian Ministry of Education.10 Teachers in these other programs were also not trained to perform first aid or make referrals.

1. **Study Setting**
   1. **Identify the sites or locations where the research will be conducted.**

This study will be conducted in 14 primary schools in Lusaka district, Zambia.

- 1. **Describe the Principal Investigator’s experience conducting research at study site(s) and familiarity with local culture**The PI has extensive experience in Zambia. He has been conducting research there since 2009, and has established a close working relationship with partners at the University of Zambia as well as the Ministries of Education and Healthth.
  2. **Is the research conducted outside the United States?**

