Fourteen community schools will be involved in the study. In each school, three grades will be selected for the study; in treatment schools, two grades will be randomly selected among those directly taught by SHWs; the grades in the control group will be chosen to match the ones in the treatment group. To be able to link health status directly to standardized tests, all students in grade 7 will be invited to participate in the study in the 14 schools. Intervention schools will receive the SHW Program as well as baseline, midline, and endline health screenings. For each of the seven schools, we will identify a control school within Lusaka district. Control schools will be chosen based on the overall school size, number of pupils in each grade, and average test score performance.

*Outcome measures*
The primary outcome of the study will be child health (prevalence of acute and chronic infection at endline) as well as academic performance (school attendance and grade performance).

The quantitative assessments at baseline, midline and endline will be complemented by qualitative work. For the qualitative component, we will employ a non-probabilistic, stratified purposeful sampling methodology. In our study we will capture the opinions of SHWs, school administrators, mothers and children from a sample of community schools with the SHW program. We will use a mixture of qualitative research methods, namely semi-structured individual interviews and focus group discussions (FGDs).

We will sample a total of 10 SHWs across the seven intervention schools. Of the schools selected, we will randomly sample 3 schools for additional investigation. From this pool of 3 schools we will conduct individual interviews with the school administrators (preferably the headmaster), and FGDs with mothers and children. There will be a total of 3 administrator interviews (1 per school) and 7 FGDs with mothers and children (1 per intervention school).

*Internal validity*

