In order to ensure that schools or students are not systematically different prior to the launch of the study (which could occur given the small sample sizes), classes and schools will be matched based on the overall school and class size, as well as the most recent school test performance. For each treated class, the most comparable class from the control group will be selected. A total of approximately 80 children (25-30 from each grade) will be enrolled from each school – all students in selected grades will be invited to join the study; final sample size will depend on class sizes as well as parental consent.

*Study interventions*
The study will assess (but not be directly involved with the delivery of) a combined intervention package currently implemented by a local NGO called Angels of Mercy. The program has two components:
1. The School Health Worker (SHW) Program. The aim of the SHW training is to empower teachers to recognize and refer children in need of medical attention, give basic first-aid care, and run health education lessons. Over the past year, HK/BF has worked with government officials and medical professionals in Zambia to develop a 10-day, 100-hour SHW training adapted from the Community Health Worker model. The curriculum trains teachers as front-line health workers capable of running health education lessons, recognizing and referring children in need of care, and providing first-line care.

Training sessions are facilitated by a group of health educators from the Ng’ombe Health Centre, all of whom have been certified by the Ministry of Health. The team of health educators consists of an environmental health-technician, clinician, clinic in-charge, and nutritionist. Additionally, all teachers are required to undergo twenty hours of clinical sessions at the Ng’ombe health centre, wherein they examine sick youth under the supervision of a clinical officer. Teachers receive K40 daily travel allowance (~$6) during training. The facilitation team from the Ng’ombe clinic meets with all of the SHWs at least once a month at their regular monthly meeting. During the meeting, the team is able to collect all forms from the teachers, assist the teachers to overcome challenges they have encountered, and add supplementary training lessons. The teachers are provided with a K100 monthly allowance (~$17), as well as shirts, bags, and SHW cards (which give them preferential care at the clinic).

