2. Bi-annual school based preventive health screening days. In collaboration with the Ministry of Health bi-annual health screening days will be conducted at all target community schools. All health screenings will be conducted by nurses and clinical officers from the local government health clinic and supported by trained SHWs. Parents or guardians are expected to attend screening days with their children and informed consent is required by both the child and guardian. As part of the screening, a complete physical examination is performed including urine screening for schistosomiasis, which is endemic in the region. All children receive a dose of vitamin A, mebendazole for presumptive deworming, and, if indicated, Praziquantil for schistosomiasis. Medication for simple acute ailments will be dispensed to the guardian of sick pupils upon the completion of the health screening. All students with chronic or severe ailments will be referred to the local health centre. AoM offers health screenings to all students within a class and are not limited to the students whom will participate in the study.
*Control group:* 7 schools will be used as the control group. All control schools will complete a baseline survey including height/weight, mid upper-arm circumference, and self-reported health at baseline, as well as an endline survey including a complete health screening.

- 1. **Does the study involve the collection of data/specimens (including the use of existing data/specimens)?**

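### With only 14 schools, school-clustered standard errors need a small-sample method: a nominal 5% test runs at about 6–10%, and higher if school-level covariates enter the model

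*Protocol*

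**What the plan says.** Section 5 of the protocol (Data/Statistical Analyses Plan) gives the quantitative analysis in two sentences. The first sets the comparison: "All outcome variables will be compared between treatment and control groups, controlling for baseline covariates observed". The second sets the inference: "To control for within-school correlations, all standard errors will be clustered at the school level". Neither gives an estimator variant, a reference distribution or degrees of freedom, and the number and level of the covariates are left open.

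Section 3 gives the number of clusters: "This study will be conducted in 14 primary schools in Lusaka district, Zambia". Section 4, under the control group, gives the split: "7 schools will be used as the control group". Control schools are matched, not randomised: "Control schools will be chosen based on the overall school size, number of pupils in each grade, and average test score performance". The sample-size paragraph deals with clustering only through a multiplier, "assuming a design effect of 2 as well as an attrition rate of 10% over the study period", and states neither alpha nor power.

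**The concern.** The programme is delivered to whole schools, so the treatment contrast varies only between schools. However many pupils are measured, seven schools against seven leave at most 12 degrees of freedom for it. The clustered (sandwich) variance is a large-number-of-clusters method. With few clusters it is biased downward, and a normal cutoff is too lenient. Each school-level covariate worsens both problems, because it uses up between-school information that the sandwich formula does not charge for.

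The rule is fixed for all outcomes, including the primary health outcome. Confidence intervals would be too narrow, and a programme with no effect would be declared effective more often than the nominal level implies. The protocol expects the results to inform a government decision on scaling up.

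**Working it through.** **Inputs from the protocol.** 14 schools, 7 against 7. About 80 pupils per school ("A total of approximately 80 children (25-30 from each grade) will be enrolled from each school"). Prevalence 0.50 against 0.35, design effect 2, attrition 10%.

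**Assumptions.** Two-sided alpha 0.05. ICC from the design effect: 2 = 1 + (80 − 1) × ICC, so ICC = 1/79 = 0.0127; 0.05 was also tried.

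**1. The plan's own sample size.** 14 × 80 = 1120, which agrees with "We expect a total sample size of approximately 1120 students across the 14 schools". With design effect 2 and 10% attrition, the two-proportion formula needs 756 pupils for 80% power and 1010 for 90% (814 and 1068 with continuity correction). The total is therefore enough by the normal formula. It cannot be derived from a stated alpha and power, because none is given.

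**2. Closed-form check (equal schools, no covariates, school means treated as normal).** The unscaled clustered variance is 6/7 of the unbiased variance. The usual scaling by 14/13 brings it to 6/7 × 14/13 = 12/13. The test statistic is then a t with 12 df multiplied by √(13/12).
- Normal cutoff: 1.960 × √(12/13) = 1.883, and P(|t₁₂| > 1.883) = 8.4%.
- t(13) cutoff: 2.160 × √(12/13) = 2.076, and P(|t₁₂| > 2.076) = 6.0%.

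**3. Simulation under no effect.** 8,000 runs per setting, 72 pupils per school after attrition, prevalence 0.5, school sizes equal or with CV 0.3. The normal column covers the clustered SE with and without the 14/13 scaling; the t(13) and ratio columns use the scaled SE.

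| School-level covariates | Normal reference | t(13) reference | True SD ÷ mean SE |
|---|---|---|---|
| none | 8.1–10.5% | 6.0–6.8% | 1.05–1.09 |
| two | 12.3–14.4% | 9.4–10.4% | 1.19–1.22 |
| three | 14.9–18.0% | 11.9–13.3% | 1.26–1.31 |

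A logistic model with the scaled SE and normal reference gave 8.6% with no covariate. Three pupil-level covariates alone gave 8.3–9.3% (scaled, normal). A second simulation (4,000 runs per setting) gave t(13) rates of 6–8% without school-level covariates, in settings that included a school-size CV of 0.4, and 10–14% with two or three.

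**4. Effect of matching.** The protocol gives no correlation between paired schools; 0.25 and 0.5 were assumed, with pairs ignored in the analysis.
- No covariates: 6.6% and 5.8% (normal); 4.5% and 3.6% (t(13)).
- Three school-level covariates: 13.7% and 12.2% (normal); 10.8% and 9.3% (t(13)).

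**5. Alternatives.** With zero to four school-level covariates and no pair correlation, CR2 with Satterthwaite df gave 4.3–5.2%. A school-level t-test with 14 − 2 − k df gave 4.8–5.4%.

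**6. Power for 0.50 against 0.35.** Pupils per arm after attrition: 560 × 0.9 = 504. Variance sum: 0.25 + 0.2275 = 0.4775. SE = √(0.4775 × 2 / 504) = 0.0435, so 0.15 / 0.0435 = 3.45. Power is 0.93 by the normal formula and 0.885 by the noncentral t with 12 df. By simulation (6,000 runs), two school-level covariates give 0.81 (school-level t) or 0.77 (CR2), and three give 0.76 or 0.70.

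**The case against.** The strongest reply is that the quoted sentence fixes only the level of clustering. CR2 with Satterthwaite df would satisfy it, the form asks only for a brief description, and a separate analysis plan may supply the correction. That is fair as far as it goes, and it is why the figures are tied to named references. It does not remove the point: the protocol sets this rule for all outcomes with 14 clusters, and the usual implementation is liberal under either common reference when paired schools are no more alike than others.

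Four limits stand.
- A reader might infer that the test will run at 13–18%, or that false positives will be two to three times the claimed rate. The documents do not support that. It needs school-level covariates, which the protocol never says it will use; school size, grade size and test scores are named for matching. The data-collection section lists mainly pupil-level measures. Without school-level covariates, the inflation is about 1.6–2 times with a normal reference and 1.2–1.4 times with t(13).
- Similarity within pairs lowers the rates. With t(13), no school-level covariates and the assumed pair correlations, the test is not liberal at all.
- Marked inequality of school sizes is not documented. Three grades of 25–30 give 75–90 pupils per school, although final numbers depend on class sizes and consent. The closed-form result does not depend on unequal sizes.
- A reader might also infer that the sample-size statement is wrong. It is not: no power is stated, and 0.885 exceeds the customary 80%.

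**Conclusion.** The point holds in a conditional form. If the clustering rule is applied in the usual way to 14 schools, the nominal 5% test runs at about 8–10% (normal) or 6–7% (t(13)). With two or three school-level covariates it runs at about 12–18% or 9–14%. These figures assume two-sided 5%, an ICC of 0.0127–0.05 and no extra similarity within matched pairs; such similarity lowers them, and in one configuration removes the inflation. They concern sampling error only and say nothing about confounding from the non-random choice of schools. The direction is well established, but the size depends on choices the protocol leaves open. It should be fixed before analysis; it is not a fatal flaw.

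**What to change.** Replace the clustering sentence in section 5 with:

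> Inference uses bias-reduced (CR2) school-clustered standard errors with Satterthwaite degrees of freedom. The supporting analysis is a t-test on the 14 school-level summaries with 14 − 2 − k degrees of freedom, where k is the number of school-level covariates. These covariates are named before the endline data are seen.

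State alpha and sidedness, and recompute the power sentence with the matching degrees of freedom. No fixed cap on school-level covariates is advised. In a non-randomised comparison, such a cap trades control of confounding against power, and the investigators should make that choice openly and in advance.

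The cost is wider intervals and some power: about 0.88 on 12 df against 0.93 by the normal formula, and about 0.77–0.81 with two school-level covariates. If paired schools are in fact alike and the pairs are ignored, the replacement is conservative (3.0–3.9% without covariates under the assumed correlations). No new schools, pupils or procedures are needed.

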**No: If no, skip to 7.1**

**Yes: If yes; indicate how, when, where, and by whom participants will be recruited**

All students in 3 selected grades at each school will be invited to participate in the study. Selected students will be asked to obtain their parents’ consent; students with completed consent forms will be enrolled in the study and asked to complete the baseline survey.

- 1. **Are there any materials that will be used to recruit participants, e.g., emails, posters, and scripts?**

**No** **Yes: If yes; provide a list of the materials (also include copies with the application)**

1. **Available Resources**
   1. **Describe the feasibility of recruiting the required number of participants within the recruitment period**

We do not anticipate any difficulties recruiting students. With an average of 25-30 students in each class we think that getting 75 students for each school should not be a problem.

- 1. **Describe how the Principal Investigator will ensure that a sufficient amount of time will be devoted to conducting and completing the research**

The project was designed to leave a sufficient amount of time to see impact; we have no specific deadline for finishing the research.

- 1. **Are there research staff members, in addition to the Principal Investigator?**

**No: If no, skip to** 7.5

**Yes: If yes; outline training plans to ensure that research staff members are adequately informed about the protocol and study-related duties**

The PI will work with [name], who will be the research coordinator for HSPH, and [name], who will be the local coordinator. Both have completed research training and will work closely with the PI to make sure all protocols are followed.

- 1. **Describe the minimum qualifications for each research role (e.g., RN, social worker) their experience in conducting research, and their knowledge of local study sites and culture**

All school-based assessments will be conducted by nurses hired by HealthyKids/Brighter Future and trained by the study coordinator ([name]).

- 1. **Briefly describe how the research facilities and equipment at the research site(s) support the protocol’s aims, e.g., private rooms available for interviews, etc.**

The project will directly work with primary schools to make sure all interviews with students are conducted in a separate room or private space.

- 1. **Are there provisions for medical and/or psychological support resources (e.g., in the event of incidental findings, research-related stress)?**

**No** **Yes: If yes; describe the provisions and their availability**

1. **Vulnerable Populations**
   1. **Are there any potentially vulnerable populations (e.g., children, pregnant women, human fetuses, neonates, prisoners, elderly, economically disadvantaged, employees or students of the investigator or sponsor, undocumented, terminally ill, cognitively impaired or mentally ill, etc.)?**

**No: If no, skip to** 9.1

**Yes: If yes; identify all vulnerable populations**

We will be working with school children.

- 1. **Describe safeguards to protect their rights and welfare**

Child assent and parent consent will be obtained. Data will be stored securely as to avoid a breach of confidentiality. Students will be informed that participation is voluntary, and that they can exit the study (or not answer any question they find uncomfortable) at any time.

1. **Consent Process**
   1. **Will consent to participate be obtained?**

**No: If no, skip to** 9.5

**Yes: If yes; describe the setting, role of individuals involved, timeframe(s), and steps to minimize coercion/undue influence during the consent process (at the time of initial consent and throughout the study)**

We will work with school authorities to make sure all teachers and students are informed about the study. To minimize the risk of coercion, students will asked to assent and get their parents’ consent.

- 1. **Are there any special populations?**

**No** **Yes: If yes; describe the process to obtain consent, permission or assent**

- 1. **Will consent of the participants be documented in writing?**

**Yes** **No: If no; describe the rationale for requesting a waiver or alteration of documentation of consent (and/or parental permission)**

- 1. **Will participants be provided with a copy of their signed consent form or information sheet (when a consent form is not signed)?**

**Yes** **No: If no; explain any extenuating circumstances that make it impossible or inappropriate to meet this requirement, i.e., doing so may place participants at increased risk, if inadvertently disclosed**

- 1. **Is a waiver or alteration of consent (and/or parental permission) being requested?**

**No** **Yes: If yes; describe the rationale for the request. If the alteration is because of deception or incomplete disclosure, explain whether and how participants will be debriefed (include any debriefing materials with the application)**

Parental consent will be obtained because the study participants are children.

1. **Risks**
   1. **Are there any reasonably foreseeable risks, discomforts, and inconveniences to participants and/or groups/communities?**

**No** **Yes: If yes; indicate probability, magnitude, and duration of each (note that risks may be physical, psychological, social, legal, and/or economic)**

- 1. **Identify whether any of the information collected, if it were to be disclosed outside of the research, could reasonably place the participant at risk of criminal or civil liability or be damaging to the participant’s financial standing, employability or reputation.**

We do not think that any of the information collected about these children could put them in any kind of financial or reputational risk.

- 1. **Outline provisions in place to minimize risk**

We will ensure privacy for the interviews and make sure identifiable information will be stored safely in a locked office in Lusaka. Only de-identified data will be shared electronically and analyzied.

1. **Benefits**
   1. **Describe potential benefits of study participation (indicate if there is no direct benefit)**

Children will be screened for infections as part of the study endline, and will receive treatment if infections are found.

- 1. **Describe potential benefits of the research to the local community and/or society**

The results of this study may lead to improvements in health programs implemented in schools in Lusaka and elsewhere if the government decides to scale these programs.

1. **Reportable Events**
   1. **Outline plans for communicating reportable events (e.g., adverse events, unanticipated problems involving risks to participants or others, breach of confidentiality)**

Any adverse events will be directly reported to local IRB as well as to school administrators, who will reach out to parents as needed.

1. **Research Related Injuries (this section must be completed for any greater than minimal risk research)**

